#### Phase 2 Data Collection

##### Aim 2

Feasibility data will be collected by the research team throughout the study using a tracking sheet stored on a secure institutional server. Usability and acceptability data will be collected using questionnaires completed electronically, by hardcopy, or verbally by phone in accordance with participant preference. Similar data collection procedures described in phase 1 will be used to collect questionnaire data in phase 2. Sociodemographic and diagnosis characteristics of the dyad will also be collected using a questionnaire. Similar qualitative data collection procedures used in phase 1 will be used to collect focus group data in phase 2.

##### Aim 3

*Stress-related participant-reported outcome measures* will be collected using questionnaires completed electronically, by hardcopy, or verbally by phone, depending on participant preference. *Salivary cortisol biospecimens* will be collected by participants using oral swab kits. Participants with dementia and care partners will each provide 10 samples in total. Five samples (per participant) will be collected over the course of 1 day at baseline and the remaining 5 will be collected over the course of 1 day after data collection. Participant dyads will receive sample kits by postal mail at least one week prior to the 2 data collection timepoints (baseline and after). Each dyad will participate in a telephone or Zoom session with a research team member to review how to collect saliva samples prior to the scheduled data collection timepoint. During this session, participants will be asked to not complete the sample collection if any of the following are present on the day of data collection: (1) a fever >101°F, (2) upper respiratory infection with nasal drainage, and (3) inflammation of the throat. As appropriate, an alternative day will be identified if any of these symptoms are present, or the data collection will be canceled and documented as incomplete in the study database.

A research team member will be available by phone or Zoom for participants to ask questions and receive support during the collection of salivary samples. Participants will also be able to access video instructions provided by Salimetrics [61]. Detailed methods for saliva collection and handling can be found online [62]. In brief, each Salimetrics kit contains 1 oral swab, 1 swab storage tube, and sample collection instructions. Participants peel back the protective package around the swab and place it under their tongue for 2 minutes after which it is placed into the prelabeled storage tube. The swab-containing storage tube is then placed in the refrigerator. On each measurement day (baseline and after) each participant will provide a saliva swab at waking, 30 minutes after waking, 60 minutes after waking, 1 hour before or after dinner, and 1 hour before bedtime for a total of 5 swabs per time point, per participant [63]. Care partners may assist the PLWD in collecting their samples. The swabs will be shipped to the corresponding institution’s biomarker laboratory using a prepaid package with a small ice pack, which will be picked up by FedEx personnel for delivery. Samples will be immediately frozen and stored at the biomarker laboratory at –20°C until assayed by a Salimetrics-certified laboratory. Collection and storage methods follow the assay manufacturer (Salimetrics) recommendations and have been validated [64].

#### Phase 2 Data Analysis

##### Aim 2

Descriptive statistics (means, SDs, frequencies, percentages) will be calculated for measures of usability, feasibility, and acceptability. Similar rapid qualitative analysis methods that were used in phase 1 will be used to analyze phase 2 focus group data.

##### Aim 3

Percentage of participants with data collected will be calculated for each outcome measure at each data collection timepoint. To further describe the study sample, the Neuropsychiatric Inventory, Perceived Stress Scale, and Dyadic Relationship Scale measures will be scored for each participant according to measurement scoring guidelines at each timepoint and group means (SDs) will be calculated. We will not assay the salivary cortisol specimens in this study, but will do so as a secondary analysis in a future study.

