**Methods:**

A human-centered design (HCD) approach will be used to increase the likelihood of developing an intervention that will be translatable to real-world settings. This study consists of 2 phases. The first phase will address the discover, define, and design stages of HCD using qualitative focus groups with dementia caring dyads (N=12-16 dyads). Dyadic focus groups (3-4 groups anticipated) will be convened to understand participants’ stress experiences and to co-design a stress management toolkit prototype. Rapid qualitative analysis will be used to analyze focus group data. In phase 2, the toolkit prototype will be user tested for 2 weeks in a new sample to address the validation step of HCD. A within-subjects (n=10 dyads), pre-post design will be used with measures of usability (frequency of toolkit use), feasibility (enrollment and withdrawal rates, adverse events/injuries), and acceptability (satisfaction, benefit) collected via questionnaires (at the end of weeks 1 and 2 of user testing) and focus groups (n=3-4 dyads/group at the end of week 2). The feasibility of collecting participant-reported, stress-related outcomes (neuropsychiatric symptoms of dementia, caregiver stress, dyadic relationship strain) and salivary cortisol as a physiologic measure of stress will be assessed at baseline and after user testing.

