### Phase 2: Validate (Aims 2 and 3)

Phase 2 will address the *validate* step of the HCD process (Table 1). A total of 10 dyads (who were not involved in phase 1) will use the prototype toolkit for 2 weeks and measures of usability, feasibility, acceptability, and stress-related outcomes will be collected (Figure 1).

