#### Phase 2 Participants and Recruitment

Similar eligibility criteria will be used in phase 2 as were used in phase 1 with few additional criteria to address contraindications to the collection of salivary cortisol biospecimens. In addition to the phase 1 criteria, participants will be excluded if they (1) currently receive cytokine-based therapy; (2) currently receive radiation therapy to the salivary glands or thyroid; (3) are diagnosed with Cushing or Addison disease. Dyads will also be excluded in phase 2 if they participated in phase 1. The same recruitment strategy used in phase 1 will be used in phase 2 as well. Ten dyads was selected as the projected sample based on prior studies that have used HCD with this population [26,27], but up to 20 may be enrolled if data saturation is not reached.

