#### Phase 2 User Testing Procedures

Dyads will receive a toolkit and toolkit user guide by mail after collection of baseline data. Dyads will participate in an introduction session with a trained research team member via Zoom or phone to review how to use the toolkit. Dyads will use the toolkit in the home for 2 weeks. A 2-week duration was selected based on prior home-based studies with this population that have used HCD [48,49]. Dyads will be encouraged to use at least one tool from the toolkit at least once a day to manage day-to-day stress and to mitigate the risk of negative outcomes related to excess stress.

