*Stress-related participant-reported outcomes* (eg, neuropsychiatric symptoms of dementia, caregiver stress, dyadic relationship strain) measured using psychometrically sound measurement tools [32,42,45] and *salivary cortisol biospecimens* of participants with dementia and care partners [58] will be collected at baseline and after user testing (Figure 1 and Tables 3 and 4). Outcome measure collection will be feasible if the measure can be collected in 80% or more of participants at baseline and after data collection timepoints.

**Table 3 table3:** Phase 2 outcome measures for aim 2.

Outcome	Measure	Measurement	Data collection tool
Usability	Frequency of toolkit use	How many days in the past week was the toolkit used by the participant with dementia/care partner? (range 0-7 days)	Questionnaire
Feasibility	Enrollment rate	Percentage of participants enrolled	Study tracking sheet
	Withdrawal rate	Percentage of participants that withdraw	
	Adverse events/injuries	Number of adverse events and injuries	
Acceptability	Satisfaction	Toolkit satisfaction scale (1=not satisfied at all to 5=very satisfied)	Questionnaire
	Perceived benefit	Toolkit benefit scale (1=not at all beneficial to 5=very beneficial)	

**Table 4 table4:** Phase 2 outcome measures for aim 3.

Outcome	Measurement	Psychometric properties	Data collection tool
Neuropsychiatric symptoms of dementia	Neuropsychiatric Inventory-Questionnaire [34]	Cronbach α (range)=.71-.88 Percentage agreement between raters: 93.6%-100% Test-retest reliability range (r)=0.79-0.86 [34,59,60]	Questionnaire
Caregiver stress	Perceived Stress Scale [43]	Cronbach α (range)=.75-.82 External validity established through CFA^a^ [42,44]	Questionnaire
Dyadic relationship strain	Dyadic Relationship Scale [45]	Cronbach α (range)=.84-.89 External validity established through CFA [45]	Questionnaire
Physiologic stress	Salivary cortisol biospecimens	N/A^b^	Oral swab

^a^CFA: confirmatory factor analysis.

^b^N/A: not applicable.

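### Aim 3 computes collection separately at each timepoint, so it cannot show whether 80% of participants have both baseline and post-test data

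*Protocol article*

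**What the plan says.** The Abstract (Methods) describes Phase 2 as a pre-post comparison within the same people: "A within-subjects (n=10 dyads), pre-post design will be used". The planned sample is 10 dyads, hence 20 individuals. Phase 2 Participants and Recruitment adds "but up to 20 may be enrolled if data saturation is not reached", so the maximum is 40 individuals.

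Phase 2 Measures, Aim 3, sets the only numerical criterion for that aim: collection of a measure is feasible "if the measure can be collected in 80% or more of participants at baseline and after data collection timepoints". It does not say whether the 80% must be the same people at both timepoints.

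Phase 2 Data Analysis, Aim 3, gives the calculation: "Percentage of participants with data collected will be calculated for each outcome measure at each data collection timepoint". The questionnaire scores are then summarised as group means and SDs at each timepoint, and the saliva specimens are stored and not assayed in this study. The article nowhere defines a percentage of participants with data at both timepoints.

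Two procedures affect who is missing and when. Phase 2 User Testing Procedures states: "Dyads will receive a toolkit and toolkit user guide by mail after collection of baseline data". Phase 2 Data Collection, Aim 3, says that illness on a saliva day leads to an alternative day, "or the data collection will be canceled and documented as incomplete in the study database".

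**The concern.** The criterion names both timepoints, but the analysis produces two marginal percentages. These give no count of people with both measurements unless they are very high or one falls below 80%. In a pre-post design, the pair is what a later change analysis would draw on.

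Aim 3 exists to inform the choice of measures for a future efficacy study. A measure could be reported as feasible on two figures of 80% while clearly fewer than 80% of participants have a usable pair. Cortisol is the plainest case. The grounds for not collecting saliva (fever, upper respiratory infection with nasal drainage, throat inflammation) are transient and can affect different people on the two days. The article does not say that a cancelled baseline day removes the participant.

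**Working it through.** The 80% is a chosen threshold with no derivation, so there is no stated figure to reproduce. The check is what two 80% margins imply for pairs.

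**Inputs.** Threshold 80% (Phase 2 Measures, Aim 3). Sample: 10 participants per role or 20 individuals as planned (Phase 2: Validate), and 40 individuals at the maximum (Phase 2 Participants and Recruitment).

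**Step 1: bounds on the paired share.** Let p1 and p2 be the proportions collected at baseline and post-test.
- Minimum with both = max(0, p1 + p2 - 1) = 0.80 + 0.80 - 1 = 0.60.
- Independent misses: p1 × p2 = 0.80 × 0.80 = 0.64.
- Nested misses (the same people both times): min(p1, p2) = 0.80.

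| n | needed for 80% | minimum pairs | pairs if nested |
|---|---|---|---|
| 10 | 8 | 8 + 8 - 10 = 6 | 8 |
| 20 | 16 | 16 + 16 - 20 = 12 | 16 |
| 40 | 32 | 32 + 32 - 40 = 24 | 32 |

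For n = 20, 4 missed only at baseline and 4 others missed only at post-test gives 80% and 80% with 12 pairs. The same 4 missed both times gives 80% and 80% with 16 pairs. The planned output is identical in the two cases. If both margins are exactly 16 of 20 and the overlap is random, there are 12 pairs with probability 0.376 and 13 with probability 0.462.

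**Step 2: when the margins are enough.** Pairs are certain to reach 80% only if p1 + p2 - 1 ≥ 0.80, that is p1 + p2 ≥ 1.80 (for example 90% at each timepoint). If either margin is below 80%, pairs are certain to fall short. In between, the planned figures do not decide the question.

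**Step 3: how much stricter a paired rule is.** Assume a per-visit collection rate p (the article gives none), with misses independent between visits and between individuals. With r the count needed for 80%:
- two separate checks: [P(Bin(n, p) ≥ r)]²
- paired rule: P(Bin(n, p²) ≥ r)

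| assumed p | n = 20, separate | n = 20, paired | n = 10, separate | n = 10, paired |
|---|---|---|---|---|
| 0.85 | 0.689 | 0.311 | 0.673 | 0.445 |
| 0.90 | 0.916 | 0.673 | 0.865 | 0.708 |
| 0.95 | 0.995 | 0.961 | 0.977 | 0.934 |

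These are illustrations under independence. With nested misses, the paired rule passes whenever the two separate checks do.

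**Step 4: dyads, only where both members are measured.** Four cells (two members, two timepoints) at 80% each guarantee 4 × 0.80 - 3 = 0.20 of dyads complete, or 2 of 10. Under independence the share is 0.80⁴ = 0.41, about 4 of 10. This applies to saliva, which both members provide, and to the Dyadic Relationship Scale if the two versions listed for phase 1 in Table 2 are both used in phase 2. It does not apply to neuropsychiatric symptoms or caregiver stress, each of which concerns one member (Table 4).

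**The case against.** Five points can be made against the concern.

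- **The criterion can already be read jointly.** This stands as a reading. It does not remove the problem, because the analysis section never computes the joint figure. A reader might infer that the protocol declares feasibility from two separate margins; the article does not settle that.
- **60% is an extreme bound.** This stands. It requires that the people missed at baseline and those missed at post-test do not overlap at all. Toolkits go out after baseline collection, and withdrawal during user testing would mainly lose post-test data. If loss occurs only after baseline, the paired share equals the post-test share. The alternative saliva day reduces misses further. The gap is possible, above all for saliva, but the documents do not show that it is likely.
- **Nothing in this study uses pairs.** This also stands. Scores are summarised by timepoint and cortisol is not assayed. A reader might infer that the study's own results would be undermined; they would not be.
- **A later trial need not rely on complete pairs.** Future Directions names a larger randomized trial without giving its analysis, and longitudinal models can retain people with one missing timepoint. No required number of pairs is stated, so the documents do not support saying that there would be too few. They support only saying that the number would not be reported.
- **Exact counting rules may sit in the full protocol.** That would cover missing detail. Here the article states both the criterion and the calculation, and the two do not match on the joint reading.

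**Conclusion.** The point holds as a low-cost improvement to the reporting and wording of Aim 3's criterion; no planned result is invalid. With 80% at each timepoint, pairs lie between 60% and 80% (12 to 16 of 20 individuals, 6 to 8 of 10 in one role), and the planned percentages cannot say where. The bounds are arithmetic and need no assumption. The 64% and the pass probabilities assume independent misses, and the pass probabilities also assume a per-visit collection rate.

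The effect is confined to the feasibility conclusion and to measure selection for the future trial. The incomplete-dyad figures should not be generalised to all four outcomes.

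**What to change.** - In Phase 2 Data Analysis, Aim 3, add: for each measure, and by role (person with dementia, care partner), the percentage of participants with data at both baseline and post-test will be calculated. Keep the per-timepoint percentages as description.
- In Phase 2 Measures, Aim 3, state that the 80% criterion is judged on that both-timepoints percentage.
- For measures taken from both members (saliva, and the Dyadic Relationship Scale if both versions are used), also report the percentage of dyads with both members complete at both timepoints.

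**Cost.** One or two sentences, using records that the study will already hold. The real price is a stricter criterion. If misses fall on different people, the difference is material: for n = 20 with independent misses and an assumed 90% collection per visit, the probability of passing is about 0.67 against 0.92 for two separate checks. If the authors intend 80% per timepoint and do not want to tighten it, they should say so in the criterion and still report the paired percentage beside it.

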### Ethics Approval

This study was approved by the Duke Health System Institutional Review Board (HUM00186832).

## Results

This study received IRB approval in August 2022 and is anticipated to be completed by July 2024. Expected outcomes of phase 1 are a working prototype of a dyadic stress management toolkit for PLWD and their care partners. Phase 2 will yield preliminary data to support the feasibility and acceptability of the toolkit, as well as data to inform the design (eg, measurement selection, recruitment, data collection methods) of a future study to examine efficacy. The goal is that by using an HCD approach that incorporates stakeholder engagement at the onset of development, this intervention will be more applicable and acceptable to families living with dementia. Exploring feasibility and acceptability in the early stages of intervention development will help determine whether costlier efficacy testing is warranted [65]. Data generated from this study will act as a stepping stone in the development of a stress management intervention for dementia caring dyads that has an increased likelihood of being implemented and sustained in the future.

## Discussion

### Expected Findings

The need for home-based stress management interventions for PLWD and their care partners was amplified by the COVID-19 pandemic [29,66]. Tangible stress management tools exist that are passive in nature (eg, low user burden, minimal training required) and safe for use by older adults, but there remains a paucity in research focused on the use of such tools by PLWD and their care partners. Furthermore, no prior studies have focused on combining multiple tangible tools to promote stress management among community-dwelling dementia caring dyads. Findings will expand state of the science by developing and user testing a tangible stress management toolkit for dementia caring dyads using an HCD approach. Qualitative findings pertaining to usability, feasibility, and acceptability will elucidate areas to refine the toolkit. In addition, insights relating to participants’ attitudes toward the cost of toolkits will provide preliminary information pertaining to the scalability of this intervention. Examining the feasibility of collecting several stress-related outcome measures will also inform measurement selection in a future efficacy study. This study will yield a working prototype of the stress management toolkit, as well as preliminary data to support the feasibility and acceptability of the intervention.

This study incorporates several innovative components including the use of HCD. HCD involves identifying problems, co-designing solutions with key stakeholders, and user testing solutions with end users early in the intervention development process. HCD is a promising approach to identifying solutions for families living with dementia as many nonpharmacologic interventions have demonstrated limitations in broader implementation and sustainability in this population. A second innovation is the inclusion of salivary cortisol samples as a biologic measure of stress. Few nonpharmacologic intervention studies have examined intervention effects from a physiologic stress-response perspective. This study will help determine whether salivary cortisol is a feasible outcome to include in a future study to determine efficacy of the toolkit intervention, as well as other intervention studies focused on community-dwelling dementia caring dyads. Strengths of this study are the use of predefined measures of usability, feasibility, and acceptability; a national recruitment strategy; multiple stakeholder engagement strategies; and remote and in-home data collection methods. Offering multiple ways to engage in this study provides a more equitable approach by circumventing barriers to support service access and research participation (eg, rurality, transportation, limited internet access).

Potential limitations of this study include issues relating to recruitment and measurement. Stress and stress management experiences and preferences are dependent on individual customs, cultures, and historical and social contexts. Thus, the specific components of the toolkit will depend greatly on the individual experiences of participants in phase 1. Although we will use a national recruitment strategy with the intent of recruiting a diverse sample in terms of sociodemographic, disease, and caregiving characteristics (eg, race/ethnicity, rurality, dementia type, relationship between dyad), it is likely that the prototype will be more relevant to some dyads compared with others. Throughout the design process we plan to incorporate multiple opportunities to personalize the toolkit based on individual and dyadic preferences to enhance generalizability and applicability. In terms of measurement limitations, many of the proposed measures in phase 2 are based on self or proxy report, which carries an innate potential for biased responses. This is particularly significant for measures of usability and acceptability of the toolkit as prior studies demonstrate discrepancies in perceived versus actual use of self-care interventions, and an increased risk of providing socially acceptable responses on satisfaction surveys [67,68]. To address this concern, we will include verbiage in questionnaire directions and verbally encourage participants to provide honest responses to these measures. We will reassure participants that they will not be judged or treated differently based on the responses they provide. The small sample for this study is congruent with feasibility study design guidelines; however, findings will be limited in terms of generalizability and future testing will be needed to determine efficacy. These limitations notwithstanding, this study is well positioned to provide the necessary data to inform the design of a successful pilot efficacy trial in the future.

